## Abstract

**Background:**

Maternal immunization confers passive immunity to the fetus by transplacental antibody transfer. Infants may be better protected against pertussis if the mother received a diphtheriae, tetanus and acellular pertussis (Tdap) vaccination in the second trimester of pregnancy compared to the third trimester. This study evaluates IgG antibody concentrations in term and preterm infants at birth and 2 months after birth after maternal Tdap-vaccination between 20^0^ and 24^0^ w of gestation vs third trimester Tdap-vaccination. Further aims are assessing the determinants that underlie acceptance of second trimester maternal Tdap-vaccination as well as the tolerability of vaccination.

**Methods:**

This prospective cohort study consists of two parts. In the acceptance part, pregnant women complete a questionnaire on determinants that underlie acceptance of a second trimester Tdap-vaccination, which is offered subsequently between 20^0^ and 24^0^ w of gestation. Vaccinated women complete an additional questionnaire on vaccination tolerability. Vaccinated women may also participate in the immunogenicity part, in which blood is drawn from mother at delivery and from infant at birth and 2 months after birth. Women are also eligible for the immunogenicity part if they received a Tdap-vaccination between 20^0^ and 24^0^ w of gestation via the national immunization program and get hospitalized for an imminent preterm delivery. Blood sampling continues until 60 term and 60 preterm mother-infant-pairs have been included. Pertussis-specific IgG antibody concentrations are determined in serum using a fluorescent bead-based multiplex immunoassay. For term infants, non-inferiority in IgG antibody concentrations against pertussis toxin (anti-PT) will be assessed referred to a historical control group in which mothers were Tdap-vaccinated between 30^0^ and 32^0^ w of gestation. For preterm infants, non-inferiority of anti-PT IgG concentrations is referred to as 85% of infants having ≥ 20 international units/mL at 2 months after birth.

**Discussion:**

This study investigates acceptance, tolerability and immunogenicity regarding maternal Tdap-immunization between 20^0^ and 24^0^ w of gestation. Its results provide insight into the effects of second trimester Tdap-vaccination on IgG antibody concentrations in term and preterm infants before primary infant vaccinations. Results on acceptance and tolerability guide antenatal care providers in communication with pregnant women and maintain the safety of second trimester Tdap-vaccination.

*Trial registration*: EU Clinical Trials Register, 2018-002976-41, retrospectively registered 24 July 2019, https://www.clinicaltrialsregister.eu/ctr-search/search?query=2018-002976-41.

**Supplementary Information:**

The online version contains supplementary material available at 10.1186/s12879-021-06559-w.

## Background

Pertussis is a respiratory infectious disease caused mainly by *Bordetella pertussis*. Especially young infants are at increased risk of severe complications, hospitalization and sometimes even death [1]. Infant vaccinations against pertussis started around 1950 with steady high coverage, leading to lower incidences [2, 3]. However, in the nineties of the previous century, pertussis re-emerged in many countries, including the Netherlands [4]. Incidences in all ages increased with epidemic peaks every 3–4 years (Fig. 1) [5].

**Fig. 1 Fig1:**
[figure not shown]
Number of pertussis notifications per 100,000 per age category in 2005–2019 [31]

The Netherlands implemented several changes in the national immunization program in response to the increase. In 1999, the first pertussis containing vaccination was scheduled at 2 months (m) instead of 3 m. Late in 2001, an acellular pertussis component was added to the preschool diphtheria, tetanus and poliomyelitis booster dose at 4 years (y) of age and from 2005 onwards, the primary infant pertussis vaccinations also contained an acellular pertussis component instead of whole cell pertussis. However, surveillance data show that the incidence in young infants did not decrease following these changes (Fig. 1) [5]. In fact, an increase within this vulnerable age group was observed during every epidemic peak [2]. Adolescents and adults are likely a source of transmission to young infants [6].

In 2011, increased incidence rates of reported pertussis cases were followed by a large outbreak in 2012 in the Netherlands and surrounding countries, including England [7]. In response to an increasing number of pertussis related deaths, the English government decided to offer a maternal pertussis vaccination by means of a tetanus, diphtheria, acellular pertussis and poliomyelitis (Tdap-IPV) vaccine to all pregnant women during the third trimester. Maternal vaccination induces protection of young, not yet (fully) vaccinated infants. It confers passive immunity to the fetus by transplacental antibody transfer, which starts around 17 weeks (w) of gestational age (GA) and peaks in the third trimester [8]. After birth, maternal antibodies wane rapidly over time [9].

The uptake in England ranged around 70% and observational data showed a high vaccine effectiveness without any important safety concerns [9, 10]. To date, over 25 countries recommend maternal pertussis immunization with reassuring effectiveness and safety data. In December 2015, the Health Council of the Netherlands advised to offer a pertussis vaccination to all pregnant women in their third trimester [11]. In July 2018, the Ministry of Health, Welfare and Sports, decided to follow the advice of a maternal pertussis vaccination program. First vaccinations were offered mid December 2019.

Most countries offer third trimester Tdap-vaccination because of its benefits for newborns in general. However, preterm infants are less protected by third trimester Tdap-vaccination due to too short time intervals between vaccination and delivery. This was demonstrated in data from England, showing that preterm infants were overrepresented in pertussis hospitalizations and with an increase from 9.8 to 12.1% in the share of preterm infants after the introduction of third trimester Tdap-vaccination [12]. A similar overrepresentation of preterm infants among pertussis hospitalizations is shown in Norway (10.0% vs 5.2%) [13] and in the Netherlands (11.8% vs 7.8%) [14]. To offer women more opportunities for vaccination, England widened the interval for maternal Tdap-vaccination to the second trimester [15], resulting in an increase of the vaccination coverage of about 15% [16]. The overrepresentation of pertussis in preterm infants in England reduced strongly since widening this interval [17]. Switzerland also recommends vaccination from second trimester onwards and showed that infants of second trimester vaccinated mothers had higher antibody levels at birth than infants of third trimester vaccinated mothers [18]. Importantly, they also showed that preterm infants of second trimester vaccinated mothers had higher pertussis antibody levels at birth than preterm infants of third trimester vaccinated mothers [19]. By contrast, Winter et al. demonstrated that third trimester Tdap-vaccination was more effective in preventing clinical pertussis than vaccination earlier during pregnancy (85% vs 64%) [20]. However, both studies used different endpoints, i.e. Eberhardt et al. used immunogenicity as outcome measure, while Winter et al. used effectiveness as outcome measure. In the Netherlands, Tdap-vaccines are offered to pregnant women from 22 w GA onwards and administered via youth public healthcare services. Studies show that women in their second trimester are less willing to accept the vaccination compared to women later throughout gestation [21, 22]. However, these studies were performed without current knowledge that preterm infants are worse off than term infants following third trimester pertussis vaccination.

We set up this study of pregnant women and their infants to fill the knowledge gap on the effects of second trimester maternal Tdap-vaccination for the prevention of pertussis in term and preterm infants. In a prospective study that is divided into two study parts, i.e. acceptance and immunogenicity, we aim to assess the determinants that underlie acceptance of Tdap-vaccination in the second trimester of pregnancy and how second trimester Tdap-vaccination induces maternal antibody levels in term and preterm infants before primary vaccinations. Furthermore, we aim to assess tolerability of a maternal Tdap-vaccination.

## Methods/design

### Study design and objectives

This study is conducted as a prospective cohort study of pregnant women, with follow-up of their infants up to 2 m of age. It is divided into two parts. In the acceptance part, determinants that underlie acceptance of second trimester Tdap-vaccination are assessed using a questionnaire, as followed up by the tolerability after vaccination. In the immunogenicity part, pertussis-specific IgG antibody concentrations are determined in term and preterm infants at birth and 2 m after birth if the mother accepted the vaccination between 20^0^ and 24^0^ w GA.

#### Primary objectives

##### Immunogenicity part

To evaluate non-inferiority of anti-Pertussis Toxin (PT) IgG antibodies in term infants at 2 m of age born of mothers who received a Tdap-vaccination between 20^0^ and 24^0^ w GA, compared to a reference anti-PT IgG at 2 m of age in a historical control group of term infants born of mothers who were vaccinated between 30^0^ and 32^0^ w GA in the period January 2014 to February 2016.To evaluate non-inferiority of anti-PT IgG in preterm infants at 2 m of age born of mothers who received a Tdap-vaccination between 20^0^ and 24^0^ w GA, as referred to at least 85% of preterm infants having anti-PT IgG concentrations ≥ 20 international units (IU)/mL as used in many immunogenicity studies.

#### Secondary objectives

##### Acceptance part

To assess pregnant women’s social cognitive determinants and underlying beliefs on maternal Tdap-vaccination between 20^0^ and 24^0^ w GA and distinguish results among women who are pregnant for the first time, women who were pregnant before, and in both groups, women with and without a known increased risk of preterm delivery.To assess the correlation between social cognitive determinants and underlying beliefs and actual behavior, i.e. acceptance of a maternal Tdap-vaccination between 20^0^ and 24^0^ w GA.To compare social cognitive determinants and underlying beliefs of maternal Tdap-vaccination between 20^0^ and 24^0^ w GA with those of third trimester maternal vaccination.

##### Tolerability (extension of the acceptance part)

To assess tolerability of the maternal Tdap-vaccination, administered to pregnant women between 20^0^ and 24^0^ w GA.To assess possible adverse pregnancy outcomes of maternal Tdap-vaccination between 20^0^ and 24^0^ w GA.

##### Immunogenicity part

To compare pertussis specific IgG concentrations at 2 m of age (i.e. before the primary infant vaccinations) between term and preterm infants.To compare the decay in pertussis-specific maternal IgG concentrations in the first 2 m after birth between term and preterm infants.To compare pertussis-specific IgG concentrations at delivery between mothers who delivered term and preterm.To compare pertussis-specific IgG concentrations in mothers who received second trimester Tdap-vaccination and a group that received third trimester vaccination.To determine levels of pertussis-specific IgG transferred from the mother to the neonate relative to the interval from vaccination to delivery, if possible depending on the variation in interval.

### Study population and setting

The study population consists of pregnant women who receive primary, secondary or tertiary antenatal care. Participants are included by their antenatal care provider and followed-up prospectively in both the acceptance and immunogenicity study parts. By including women in secondary and tertiary care, we aim to oversample women with an increased risk for preterm delivery, e.g. women with multiple pregnancy, history of preterm delivery, cervical conization in the medical history and uterus anomaly.

In order to be eligible to participate in this study, women must be 18 y or older, pregnant, and in relation to the immunogenicity part of the study, both parents (or mother and legal guardian) must be willing to adhere to the protocol and perform all planned visits and sample collections for themselves and their newborn child. Women who meet any of the following criteria are excluded from participation in the immunogenicity part of this study: history of having received a pertussis containing vaccination in the past 2 years; known or suspected serious underlying condition that can interfere with the results of the study such as but not limited to cancer, autoimmune disease, immunodeficiency, seizure disorder or significant psychiatric illness; receipt of any high-dose (≥ 20 mg of prednisone daily or equivalent) daily corticosteroids within 2 weeks of study entry (inhaled or other local steroids are acceptable) with exception of corticosteroids to enhance maturation of fetal lungs in case of imminent early delivery; receipt of other immune modulating medication, for instance biologicals; receipt of blood products or immunoglobulins, within 3 months of study entry (rhesus negative women who receive anti-rhesus (D) immunoglobulin will not be excluded from the study); presence of bleeding disorder; having experienced a previous severe adverse reaction to any vaccine; receipt of any vaccine(s) within 2 weeks of study vaccine (except influenza vaccine which may be given concomitantly); all mothers who give birth before 24^0^ w GA.

### Recruitment and follow-up

In the acceptance part, women complete an online questionnaire on the determinants of acceptance of second trimester Tdap-vaccination. The vaccine is offered between 20^0^ and 24^0^ w GA and administered by their antenatal care provider if accepted. Vaccinated women complete a second questionnaire on the tolerability of vaccination. They are also eligible for participation in the immunogenicity study part. In this part, a blood sample from the mother and infant (cord blood) is drawn at delivery and a second sample from the infant at 2 m of age, i.e. before the first infant vaccination. Study samples are stored at the laboratory of the National Institute for Public Health and the Environment. Recruitment continues until blood samples are drawn from 60 term and 60 preterm mother-infant-pairs.

During the recruitment phase, two alternative recruitment routes were added to increase inclusion speed for both study parts (Fig. 2). The alternative acceptance route focuses on recruitment of women for the acceptance part via midwives in primary care facilities. The alternative immunogenicity route focuses on faster recruitment of preterm infants via secondary and tertiary antenatal care.

**Fig. 2 Fig2:**
[figure not shown]
Participant recruitment and alternative recruitment routes in antenatal care in primary care facilities or hospitals

#### Alternative acceptance route

After completing the questionnaire on the determinants that underlie acceptance of second trimester Tdap-vaccination, midwifes inform pregnant women about the possibility of getting a Tdap-vaccination via youth public healthcare services. Vaccination status is requested retrospectively via the national immunization registry. The vaccine is not administered by the antenatal care provider in this route.

#### Alternative immunogenicity route

Antenatal care providers in hospitals ask consent for sampling cord blood and finger-stick-blood if a women gets hospitalized for an imminent preterm delivery and proves that she received a Tdap-vaccination between 20^0^ and 24^0^ w GA via the national immunization program. In case of an unclear answer, vaccination status is requested retrospectively via the national immunization registry. Further study procedures for blood sampling are identical to those in in the immunogenicity part.

### Questionnaires

#### Acceptance

The online questionnaire focuses on behavioral determinants and beliefs that underlie acceptance of a second trimester Tdap-vaccination. It consists of about sixty questions and statements assessing demographics, social cognitive determinants, underlying beliefs, past experiences, women’s information desires and considerations regarding information provision and implementation of maternal Tdap-vaccination. A Dutch version of the questionnaire is provided in Additional file 1: Appendix 1.

#### Tolerability

This questionnaire contains questions about the onset of local reactions and solicited systemic adverse events (AE) within 1 week post-vaccination. Local reactions include swelling, redness, and pain at the injection site. Systemic AEs include fever, headache, tiredness, nausea, vomiting, diarrhea, dizziness, loss of appetite, stiffness of muscles and joints, itch, abnormal sweating, skin rash, swollen lymph nodes, sore throat, upper airway infection, coughing, fainting, and influenza-like illness. The questionnaire also includes questions about solicited systemic events at baseline, i.e. in the week pre-vaccination. Time interval and duration of symptoms are collected, as well as the use of analgesics, medical intervention, and absence from work and/or other activities. A Dutch version of the survey is provided in Additional file 2: Appendix 2.

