### Investigational product

Boostrix is a suspension for injection in a prefilled syringe containing diphtheria, tetanus and acellular pertussis vaccine (adsorbed, reduced antigen content). The Boostrix vaccine will be given as a single 0.5 mL intramuscular injection, in the deltoid muscle of the upper arm between 20^0^ and 24^0^ w GA. For subjects who are ill or have a moderate or high fever (rectal temperature of > 38.0 °C), vaccination will be postponed until the symptoms of illness and the fever have disappeared. Pregnant women in the historical cohort [24] received the same vaccine investigational product.

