#### Tolerability (extension of the acceptance part)

The percentage and 95% CI of pregnant women experiencing adverse events (AE) within 1 week after Tdap-vaccination are described by type and severity of the AE. Using binary generalized mixed models (GLMM), the association between the occurrence of symptoms in the week before and the week after vaccination will be analyzed. Proportions of absence from work and/or other activities, and medical intervention within 7 days after vaccination will be calculated together with 95% CI as well as the association of these items before and after vaccination using GLMM.

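### The pre-vaccination control week appears to be recalled on the post-vaccination questionnaire, and postponement for illness also shapes it, so the before-after tolerability contrast is not like with like

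*Protocol article*

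**What the plan says.** The Protocol article, Recruitment and follow-up, sets out two questionnaires. The first, on acceptance, comes before the vaccine is offered. The vaccine is then "administered by their antenatal care provider if accepted", with no placebo or blinding, and "Vaccinated women complete a second questionnaire on the tolerability of vaccination".

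Questionnaires, Tolerability, describes that second form. For the risk week: "This questionnaire contains questions about the onset of local reactions and solicited systemic adverse events (AE) within 1 week post-vaccination". For the control week: "The questionnaire also includes questions about solicited systemic events at baseline, i.e. in the week pre-vaccination". The solicited list includes fever and ends with "sore throat, upper airway infection, coughing, fainting, and influenza-like illness". The section adds that the time interval and duration of symptoms are collected, without saying for which week. It refers to Appendix 2 for the form, which is not among the documents.

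Statistical analyses, Tolerability, plans percentages with 95% CI for the week after vaccination. It then plans a binary mixed model in which "the association between the occurrence of symptoms in the week before and the week after vaccination will be analyzed", and for absence and medical intervention "the association of these items before and after vaccination using GLMM".

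Investigational product states that, for women who are ill or have a moderate or high fever, "vaccination will be postponed until the symptoms of illness and the fever have disappeared".

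**The concern.** The woman's own week before vaccination is the only comparator described for systemic symptoms. A self-controlled comparison is sound if the two weeks are measured alike and differ only in exposure. Two features work against that.

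1. **Recall.** One form that covers the full week after vaccination and also asks about the week before appears to collect the earlier week retrospectively, over a longer interval, from a woman who knows she was vaccinated. The wording also differs: onset of events after vaccination, events before it.
2. **Postponement.** Women are vaccinated once illness or fever has cleared. Acute illness can therefore be concentrated in the control week (vaccination soon after recovery) or removed from it (vaccination later). The risk week is not selected in this way.

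The mixed model allows for correlation within a woman. It cannot remove differential recall or the effect of selecting women who are well on the vaccination day. The article intends the tolerability results to inform communication with pregnant women about safety. A false signal could deter women, and a masked one could falsely reassure them. The Limitations section mentions neither mechanism.

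**Working it through.** The article states no sample size, rate or effect for tolerability, so there is no figure to reproduce. Every number below is an assumption or follows from one, and there is no true vaccine effect throughout.

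**Recall**

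Let p be the true weekly symptom rate in both weeks and r the share of pre-week episodes reported, with post-week reporting complete. With probability 0.5 (assumed) a woman has the same status in both weeks; otherwise the weeks are independent. Then:

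- both weeks positive: B = p × (0.5 + 0.5p)
- reported after only: p − rB
- reported before only: r(p − B)
- within-woman odds ratio = (p − rB) / [r(p − B)]

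For p = 0.20, B = 0.20 × 0.60 = 0.12.

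- r = 0.90: (0.20 − 0.108) / (0.90 × 0.08) = 0.092 / 0.072 = 1.28. The marginal odds ratio is (0.20/0.80)/(0.18/0.82) = 1.14.
- r = 0.75: (0.20 − 0.09) / (0.75 × 0.08) = 0.11 / 0.06 = 1.83. The marginal odds ratio is (0.20/0.80)/(0.15/0.85) = 1.42.

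A mixed model estimates an odds ratio conditional on the woman, so the within-woman figures are the closer guide.

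For p = 0.10 (B = 0.055) and p = 0.30 (B = 0.195) the same formula gives the middle column below. The last column is the simulated chance that a two-sided 5% McNemar test (a stand-in for the mixed model) shows significantly more symptoms after vaccination, for 100 to 400 women. The nominal value is 2.5%.

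| Pre-week reporting r | Spurious odds ratio, p = 0.10 / 0.30 | False signal of harm, range over N and p |
|---|---|---|
| 1.0 | 1.00 / 1.00 | 2–3% |
| 0.9 | 1.25 / 1.32 | 4–24% |
| 0.8 | 1.56 / 1.71 | 9–72% |
| 0.7 | 1.95 / 2.22 | 15–96% |

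With 200 women and r = 0.8, the false-signal rate is 15% at p = 0.10 and 42% at p = 0.30.

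**Postponement**

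Assumptions: acute illness starts at 1% or 2% per day in a well woman and lasts 4 or 7 days on average. Vaccination is put off while she is ill and given 0 to 14 days after recovery. The entries are the ratio of the post-week to the pre-week rate.

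| Setting | Any illness present | New onset |
|---|---|---|
| No postponement | 0.99–1.00 | 0.98–1.01 |
| Vaccinated 0–3 days after recovery | 0.53–0.67 | 1.03–1.80 |
| Vaccinated 7–14 days after recovery | 0.98–1.09 | 1.56–2.34 |
| Postponed women left out | 0.99–1.01 | 1.56–2.27 |

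The direction thus depends on the delay and on what is counted. The last row matters for the remedy. Among women who were well on the planned day, illness is equally likely in either week: at 1% per day, 1 − 0.99^7 = 0.068 both before and after. But an onset in the week before counts only if the episode also ended before the vaccination day, so a count of onsets stays unbalanced even without the postponed women.

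**The case against.** - **Timing is inferred.** No completion date is given and Appendix 2 is not shown. A reader might conclude that the control week is certainly recalled at least a week later. The documents do not establish that; the form could be completed in parts. A single form completed after vaccination remains the natural reading, and no symptom record before the injection is described.
- **The postponement rule is narrower than it may look.** A reader might infer that women must be free of every solicited symptom when vaccinated. The rule concerns illness and moderate or high fever, and nothing says that tiredness, itch or dizziness would delay vaccination. The argument is therefore confined to fever and respiratory symptoms, and the number of women postponed is unknown.
- **The two mechanisms can oppose each other.** Poorer recall inflates an apparent effect; prompt vaccination after recovery can mask or reverse it when presence is counted. The net direction for infection-type symptoms is open.
- **Symptom timing and duration are collected.** If that covers both weeks, it helps separate carried-over illness from new onset. It does not help with forgotten episodes.
- **Little depends on the contrast.** Tolerability is a secondary objective, the post-vaccination percentages make no use of the control week, and no decision threshold is tied to the model. This limits the weight of the point but leaves the contrast open to bias.
- **Recruitment is under way.** A change now creates two baseline methods, and in the alternative acceptance route the antenatal care provider does not vaccinate. Both are fair, and the remedy has to allow for them.

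**Conclusion.** The point holds in a limited form. As described, the control week is measured differently from the risk week, and the planned model cannot correct this. Poorer recall alone would bias the contrast towards an apparent vaccine effect. Postponement makes fever and respiratory symptoms non-comparable in a direction that cannot be settled from the article.

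The size is not known. On the assumptions above, forgetting 10% of pre-week episodes gives a spurious within-woman odds ratio of about 1.25 to 1.32, and forgetting 20% about 1.56 to 1.71. These are illustrations, not estimates for this study.

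A reader might infer that the tolerability results as a whole are unreliable, or that a false signal of harm is to be expected. The documents support neither. The post-vaccination percentages and the immunogenicity objectives are untouched, and the net bias may go either way for infection-type symptoms. It is a worthwhile, low-cost improvement to one secondary analysis.

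**What to change.** - **Women still to be vaccinated by their antenatal care provider:** complete the existing pre-week items just before the injection and the post-week items at day 7, so that each week is recalled over seven days.
- **Counting:** define onset and presence identically for both weeks.
- **Postponement:** record when vaccination was put off for illness, and repeat the mixed model for fever and respiratory symptoms without those women. Base this analysis on presence in each week, since the calculation shows that a count of onsets stays unbalanced. The postponement rule itself is unchanged.
- **Baseline already collected after vaccination, or not obtainable at the visit:** analyse by baseline method, treat the before-after contrast as descriptive, and state the recall limitation.

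The cost is one form split into two parts with no new items, a short task at the vaccination visit, one sensitivity analysis, and some loss of precision from having two baseline methods. Women remain aware of their vaccination when they report the second week, so the change equalises the recall interval but does not blind the comparison.
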